#### Exclusion criteria

Life expectancy, under the physician opinion, of less than one year; diagnosis of dementia or cognitive decline that makes him/her unable to understand study information and/or sign informed consent; low capacity for self-management due to dependence on other person for medication compliance, or measuring blood pressure and daily weigh; lack of decision capacity in relation with diet or preparing meals; current participation in other clinical study; patient has no further follow-up possibilities with enrolling investigation during planned study period (such as anticipated relocation); patients with major depression and/or psychiatric medication that hinders their daily activity.

### Intervention design

#### Training sessions

The intervention will be delivered via mHealthApp and a smart band. The data related specifically to the primary and secondary end-point will be collected during regular follow-ups. During recruitment, patients will receive a smartphone the smart band and training materials. Demonstration workshops (at some hospitals) will be organized to showcase the use of the mHealthApp and resolve possible initial issues. During the intervention, technical support will be available to resolve any possible complications.

#### Possible HRQoL specific measures

##### General assessment (functioning and self-efficacy) and recurrence

All cancer survivors should be assessed at least once a year. The assessment should include symptoms related to cancer and symptoms prior to treatment. The appropriate follow-up care should be clinically indicated. This assessment can be done by the oncologist or primary care clinician.

Depending on the cancer type and stage of disease, transition of care to primary care may be done when deemed clinically appropriate, with referral back to oncologic care as needed. It is not assumed all survivorship issues are addressed at every visit. Functioning and disability are concepts in increasing use in clinical settings and in public health and much related to cancer survivorship [46]. The use of functioning as a third health indicator could offer much more than the frequency of a disease and the survival rates. From the public health perspective, it reveals information on how the population performs its activities and participation. Validated tools used to screen for long-term and late physical and psychosocial effects of cancer and its treatment survivors already exists. WHODAS 2.0 [47] is a tool to for evaluating health and functioning based on the ICF functional model. It is an alternative to the ICF whose main criticism relates to the effort required to complete. It is 36-item self-administered questionnaire (or proxy-administered) regarding disability. The WHO-DAS II measures disability in 6 domains: understanding and communicating (cognitive), getting around (mobility), self-care, getting along with people, life activities (domestic responsibilities, leisure, work), and participation in society. In addition to 36 item versions, there is also a 12-item version. It is useful for brief assessments of overall functioning in surveys [48].

The General Self-efficacy Scale (GSES) [49] is a validated self-report measure that assesses the overall impression of one’s ability to deal with demanding situations. GSES consists of 10 questions that require patients to self-evaluate, on a scale from 1 (not at all true) to 4 (exactly true), statements regarding their confidence in dealing with unexpected events [50].

Regarding screening, breast cancer imaging with annual mammography and possibly magnetic resonance imaging (MRI) is suggested for women who have been treated with RT. For those not treated with RT, age-appropriate screening guidelines should be followed. Following the NCCN2020 guidelines [37, 51] a PREM was designed as a screening tool focusing on breast cancer recurrence or new primary breast cancer. For survivors treated with RT to the abdomen, pelvis, spine, or traumatic brain injury, COG guidelines recommend surveillance with colonoscopy from age 30, with further interval screening based on clinical findings at colonoscopy.

##### Assessment of Health Related Quality of Life (HRQoL)

QoL represents a person’s perception on their position in life. It reflects the context of the culture and value system in relation to their goals, standards, and concerns. In order to assess HRQoL the European Organization for Research and Treatment of Cancer Core Cancer Quality of Life Questionnaire (EORTC QLQ-C30) [52] was selected as the relevant tool. The EORTC QLQ‐C30 is a 30‐item cancer‐specific HRQoL instrument producing a global health status, five functioning scales (physical, role, social, emotional and cognitive functions), three symptom scales (fatigue, nausea/vomiting and pain) and six single‐symptom items (dyspnoea, insomnia, appetite loss, constipation, diarrhoea and financial difficulties), but no single‐index values.

##### Assessment of cardiovascular risk

Cancer treatments can result in diverse cardiovascular issues. NCCN2020 guidelines [37, 51] focus specifically on heart failure or cardiomyopathy that may arise from anthracycline therapy. However, cardiomyopathy may be laso caused by other systemic therapies, i.e., HER2-targeted therapies and other myopathies, i.e., myocarditis [53]. Signs of cardiac dysfunction can be observed even prior to the development of symptoms [37]. If detected early the cardioprotective medications can mitigate the anthracycline-induced heart failure. However, there is only limited number of prospective studies evaluating these medications [37].

##### Assessment of lymphedema

Lymphedema, a side effect of cancer treatment, results from damage to the lymphatic system. It occurs on the same side of the body as the cancer treatment, when lymph fluid accumulates in the interstitial tissue [37, 51]. This causes swelling of the limb or other areas such as the neck, trunk, or genitals. The diagnosis of lymphedema is, in most cases, confirmed within 18 months of treatment; however, it can develop at any time in the survivor’s life [37, 51]. The cohort with higher risk of developing the lymphedema is represented by survivors that underwent surgery and/or radiation to the axillary, supraclavicular, cervical, or inguinal lymph node system [37, 51, 54]. Since stages 0 and 1 are reversible, early diagnosis is the key to optimal treatment. The stages 2 and 3, however, are less responsive to treatment. The prospective surveillance model (PSM) had been recognized as an optimal framework to guide clinical implementation of a screening methodology for early identification and management of breast cancer treatment-related impairments [55]. PSM can help in early identification and treatment of lymphedema, even in subclinical stage. In the subclinical stage, the intervention can prevent the progression to a more chronic form. According to NCCN2020 guidelines, survivors with high risk; i.e. a history of radiation or surgery to the lymph nodes, should be questioned about swelling or feeling of heaviness, fatigue, or fullness at each visit [37, 51].

##### Assessment of pain

Over one-third of post-treatment cancer survivors experience chronic pain. It often leads to psychological distress; decreased activity, motivation, and personal interactions; and an overall poor quality of life [56]. In general pain can be nociceptive or neuropathic. Somatic nociceptive pain is described as sharp, throbbing, or pressure-like. It often occurs after surgical procedures. The visceral nociceptive pain is often diffuse and described as aching or cramping [56]. Neuropathic pain is a result of an injury to the peripheral nervous system or CNS and might be described as numbness or as burning, sharp, tingling, prickling, electrical, or shooting pain. Often it develops as a side effect of chemotherapy or radiation therapy or is caused by surgical injury to the nerves. For this reason, it is very common among breast and colorectal cancer survivors. Unfortunately, there is few data on effective pharmacological treatments of CIPN.

The NCCN2020 guidelines [37, 51] make recommendations to manage the following seven categories of pain: neuropathic, chronic, myalgias/arthralgias, skeletal, myofascial pain, gastrointestinal/urinary/pelvic pain, and post-radiation pain [37]. It, however, does not include The recommendations regarding prevention and management of chemotherapy-induced peripheral neuropathy (CIPN). The recommendations for CIPN can be found in ASCO’s clinical practice guidelines [57]. Additionally, ASCO provides clinical practice guidelines for the management of chronic pain in adult cancer survivors [58]. In PERSIST the Wong-Baker FACES Pain Rating Scale [59]. It is a unidimensional intensity scale and includes the 11-point numeric rating scale from 0 (no pain) to 10 (extreme pain) accompanied with visual/word descriptors.

##### Assessment of hormonal imbalances

The NCCN2020 guidelines [51] define menopause as: (i) no menses for one year in the absence of prior chemotherapy or tamoxifen use or (ii) no menses after surgical removal of all ovarian tissue [37]. However, significant number of cancer survivors experience menopausal symptoms without meeting the above criteria. In fact, hormonal symptoms in cancer survivors have been most extensively studied in female survivors after treatment of breast cancer. Studies report that hot flashes, vaginal dryness and dyspareunia are common among breast cancer survivors [60]. Other symptoms of hormonal imbalance may be sexual dysfunction, depression, fatigue, etc. [37] From the NCCN2020 guidelines [51] we select questions targeting vaginal dryness, and urogenital complaints associated with menopause when designing the specific PREM. Other symptoms are already addressed in other measures.

##### Assessment of sexual dysfunctions

Sexual dysfunction is often caused by hormonal therapy and surgical or radiation therapy directed towards the pelvis (i.e. during colorectal cancer treatment) [37]. Depression and anxiety are commonly associated with survivorship and can further contribute to imparied sexual function [51]. Sexual dysfunctions after cancer treatment are more common in female survivors [61]. The female dysfunctions relate to issues with desire, arousal, orgasm, and pain. The problems vary depending on the cancer site and treatment modalities used. A prevalence of chemotherapy-induced menopause had been observed within the cohort of breast cancer survivors that were treated using chemotherapy [37]. Furthermore, body image changes related to breast cancer surgery and reconstruction can affect women’s sexual life and well-being [62].

Although effective strategies for treating both female and male sexual dysfunctions exists, sexual function is rarely discussed with survivors. In line with NCCN2020 guidelines [51] and EORTC QLQ-BR45 [63] we designed a 2-question PREM as a screening tool.

##### Assessment of fatigue

In order to promptly diagnose and effectively treat moderate and severe fatigue, all survivors should be screened for symptoms of fatigue [37]. Fatigue is a highly subjective experience. In order to include fatigue in clinical routine the clinicians must understannd patients’ interpretations of their fatigue level. To standardize the patient reports NCCN guideliness propose to evaluate the fatigue through three and one item severity scales [64].

##### Assessment of symptoms of anxiety

Fear of recurrence, distress, anxiety and depression are the most relevant mental health risks for cancer survivors. These risks may persist many years after diagnosis. The NCCN Guidelines provide a questionary for patient self-assessment and an algorithm for oncologists and other health care providers to screen for distress, anxiety, and depression in cancer survivors. The algorithm focuses on common mood disorders after cancer and is not intended as a psychiatric diagnosis tool [37]. For PERSIST the Generalized Anxiety Disorder (GAD-7) [65] questionnaire was chosen to assess symptoms of anxiety. It is a validated diagnosis tool implemented as a 7-item, self-report questionnaire designed to assess the patient’s status during the previous 2 weeks. The items target feelings of nervousness, anxiety, or if the patient was on edge, not being able to stop or control worrying or over-worry different things. It also measures if the patient had trouble relaxing or if patients were easily annoyed or irritable and or afraid.

##### Assessment of symptoms of depression

Symptoms of depression are pervasive in survivors. However, often the distressed survivors may not appear distressed. Therefore, all survivors should be screened for anxiety, depression, and distress, especially at times of disease transition, surveillance, significant loss, major life events, and social isolation [37]. In fact, routine screening of cancer-related distress, including clinical anxiety or depression and post-traumatic stress, should be carried out as part of the standard follow-up of survivors at least annually. Survivors with multiple or repeated somatic complaints should also be screened as part of their overall workup. However, the NCCN guidelines do not address how to detect somatic behaviors.

Patient Health Questionnaire PHQ-9 [66] and Patient Health Questionnaire PHQ-2 [67] were chosen as screening tools. The PHQ-9 is the 9-item depression module. Major depression is suspected if, in the past 2 weeks, five or more of the nine criteria have been observed at least “more than half of the days”. Additionally, one of the symptoms is depressed mood or anhedonia [68]:2. The PHQ-2 is a short version. It uses the first 2 questions of the PHQ-9 to investigate the frequency of the symptoms of depressed mood and anhedonia. Each question is scored as 0 (not at all) to 3 (nearly every day).

##### Assessment of cognitive function

The hypothesis that neurotoxicity resulting in brain white matter damage plays an important role in cognitive deficits after chemotherapy had been supported by multiple studies [69]. Functional MRI studies show that changes in brain activity accompany cognitive complaints or cognitive deficits in survivors [70]. In line with NCCN2020 guidelines [37, 51] and EORTC QLQ-BR45 [62], we designed a 3-question PREM as a screening tool. Further, as a more in-depth tool FACT-Cog [71] can be used to further assess cognitive complaints in cancer patients. FACT-Cog is a 37-item questionnaire. It measures complaints in six cognitive domains: memory, concentration, mental acuity, verbal fluency, functional interference, and multitasking ability. Moreover, the tool includes two other subscales: ‘‘comments from others’’ (i.e. ‘‘noticeability’’) and ‘‘effect of perceived cognitive impairment on quality of life’’.

##### Assessment of healthy lifestyle, nutrition and physical activity

Cancer survivors are often motivated towards self-intervention to improve their treatment outcomes, QoL, and overall survival [72]. They often seek information about dietary options and supplements, and physical activity. Namely, all cancer treatments (i.e., surgery, radiation, and chemotherapy) can significantly affect nutritional habits, alter regular eating patterns, and adversely affect how the body digests, absorbs and uses food. Following NCCN2020 guidelines [51], we designed a PREM for nutritional assessment. It comprises of questions assessing (healthy) nutrients and fluids intake, weight variation, meal frequency, and eating habits.

Further, Physical activity represents an appealing intervention. It could alleviate sequelae related to cancer and assist patients in returning to the health status they had before treatment [73]. It has positive effects in physiology, body composition, physical functions, psychological outcomes, and quality of life in patients after treatment for breast cancer [73]. To assess physical activity the Global Physical Activity Questionnaire (GPAQ) [74] was chosen as the appropriate tool. GPAQ measures the number of minutes spent in three areas, work, leisure, and transportation in a typical week, i.e., spent for walking/cycling to get to and from locations. Using this data GPAQ calculates metabolic equivalents to express the intensity of self-reported physical activities.

#### Data collection

Baseline data to be collected during or right after recruitment (T1): clinical and demographic data as well as social aspects of health status and QoL (social determinants of health). During recruitment baselines, data regarding survivor’s activation (PAM) and self-efficacy (CASE-Cancer) will be collected.

Data collection will be provided by Smart devices LZD Smart band (Fitbit like) from Naicoms and Smartphone. This data includes:data reported by patients using the mobile application – based on PROs: we will deliver and select form the following tools: Quality of life for cancer patients (EORTC QLQ‐C30), Patient Health Questionnaire-2 (PHQ-2), Patient Health Questionnaire-9 (PHQ-9), General Anxiety disorder (GAD-7), WHO Disability Assessment Schedule (WHODAS 2.0), proprietary questionnaires were designed by participating oncologists for additional risk assessment related to health-related specific symptoms related to physical symptoms, cardiovascular risks, pain, fatigue, malnutrition, lymphedema, hormonal disbalances, sexual dysfunction, gastrointestinal conditions and cognitive functioning.data from the physical activity tracker worn by the patient: Vital signs and physical activity. Blood pressure, heart rate, Blood Oxygen, Steps, Calories, Distance, Running Track, Sleep Monitor—built in the firmware of the watch.data from software sensors to be developed by UM and SYM (e.g., facial action units, acoustic features, emotion and mood estimation extracted from diary recordings).

The pseudo-anonymised data will be stored in a Big Data platform hosted in CESGA infrastructures (CESGA is a Spanish public institution offering high performance computing services for administrations and research purposes).

The data is gathered in the following way:Manually (T2 and T3)—obtain patient information using questionnaires (PROMs, PREMs and health-related questions) displayed in a Smartphone screen.Supported (T4)—the component will converse with the users using natural free speech. It will be able to engage with them in an organic dialogue by helping the user to provide answers to PROs and to health-related questions.Automated Classification (T2, T3 and T4): Speech recognition and feature extraction from recorded interaction. Facial biomarkers will be used to extract facial action points. Speech biomarkers will be used to extract acoustic features from the interaction. Text features (i.e., words, sentiment, syntax and semantics, topic and named entity classification and morphology) will be extracted from recognized speech.

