#### Primary and secondary endpoints

The primary endpoint is defined as: *increased perceived self-efficacy in participants (80 colorectal, 80 breast cancer survivors from the 4 pilot hospitals) following the mHealthApp supported intervention as measured using CASE-cancer scale for cancer as the validated standardized measure.*

The secondary endpoints include:observing modifications in patient activation levels measured using the PAM,observing modification in User acceptance depending on the level of support measured via SUS and UEQ,description of negative outcomes over time: hospitalization, exacerbations, treatment adherence, depression, recurrence, drug escalation,impact of variable modes of delivery (e.g., conversational agent) on quality of answers measure with DQS,the impact of patient trajectories (extracted from retrospective data) and PGHD on prediction of possible secondary disease or negative outcome,the impact of patient trajectories (extracted from retrospective data) and PGDH on improved intervention against the appearance of secondary diseases, worsening late toxicities or development of fatal events (sudden death, suicide).

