## Methods/design

### Study design

A single-case experimental prospective study was designed in alignment with single-case experimental design (SCED) methodology [42]. Within SCED, each individual is his/her own control group based on the first measurement prior to the intervention. The SCED was selected since single-case designs can capitalize on the ability of technology to easily, unobtrusively, and repeatedly assess health-related behavior [43]. The study design is highlighted in Fig. 1. It is based on the Changing Criterion design in which the intervention and delivery of intervention are modified through personalization of (a) goals/tasks and (b) with spoken language interfaces and embodied conversational agents to complement the regular baseline delivery mode via the digital interfaces of the mHealthApp. The study will take place between 1st of May 2021 and 31st of December 2022, with the recruitment period between 1st of April 2021 and 15th May 2021. Data collection is first carried out prior to intervention, during recruitment round (T1). Each recruited individual will sign a letter of consent and fill in CASE-cancer and PAM questionnaires. The SUS questionnaire responses, along with CASE-Cancer and PAM will be collected following a baseline phase (T2) which will last for 6 months. During this phase a ‘generic’ intervention will include a recording of the diary (at least 3 times a week), report regarding their emotional state (at least once a day) and answering a specific PRO for reporting Health Related QoL and symptoms (a different PRO each day). In total, we expect 10–15 min of interaction every day. T2 will conclude with the first follow-up with clinician, during which data regarding primary (CASE-Cancer, PAM, SUS/EUQ) and secondary endpoints will be collected. The personalized intervention phase (T3) will include execution of tasks on mHealth App personalized for the survivor. The data collection tools will remain the same, however the responsible oncologist will define which of the tools the patient must implement (e.g., which PROs) and in what frequency, depending on the risk assessment implemented by the clinical staff. During intervention, specific tools may change depending on the risks detected for the specific patient. T3 concludes with a follow-up during which data regarding primary/secondary endpoints (CASE-Cancer, PAM, SUS/UEQ). A first comparison between generic intervention and personalized intervention will be made. The AI supported clinical intervention (T4) will introduce embodied conversational agent EVA [44] and AI-drive risk assessment engine to deliver fully personalized intervention and to demonstrate that the data-driven models developed within PERSIST can improve quality of life of cancer survivors by acquiring, managing, sharing, and processing big data to create overall actionable insights at the point of care.

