#### Study itinerary

Follow-up data will include updated information on main outcomes (acceptability and usability). Specific questionnaires related with satisfaction and usefulness will be applied to patients and physicians. In addition, healthy habits, disease knowledge, self-management, QoL, and morbidity and mortality end-points will be analyzed.

The recruited patients will receive the necessary devices for the correct development of the follow-up phase of the clinical study: a smartphone and a wearable quantifying device for physical activity estimation and health parameters measurement (such as blood pressure and heart rate). The overall Implementation of the study is visualized in Table 1.

**Table 1 Tab1:** The itinerary of the single-case experimental prospective study

Study procedures	Screening/recruitment	Baseline collections (T1)	Follow up visits		
			Visit 2 (T2)	Visit 3 (T3)	Visit 4 (T4)
Informed consent	X				
Inclusion/exclusion criteria	X				
Questionnaires for Primary and Secondary endpoints		X	X	X	X
Medical history (data collection)		X			
Candidate receives a smartwatch	X				
Candidate receives a smartphone	X				

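### App-collected PROs move from on-screen answers (T2, T3) to a speaking agent that helps the user answer (T4), so a T3-to-T4 change in these scores cannot be separated from the change of answer mode

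*Protocol article*

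**What the plan says.** Data collection in the protocol article ties the answer mode to the phase. For the first two app phases the entry is "Manually (T2 and T3)—obtain patient information using questionnaires (PROMs, PREMs and health-related questions) displayed in a Smartphone screen". For the last it is "Supported (T4)—the component will converse with the users using natural free speech", with the component "helping the user to provide answers to PROs and to health-related questions". The instruments delivered through the app include the EORTC QLQ-C30, PHQ-2, PHQ-9, GAD-7, WHODAS 2.0 and questionnaires written by the participating oncologists.

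Study design brings in the conversational agent and the AI risk engine together in T4, and gives that phase the aim "to demonstrate that the data-driven models developed within PERSIST can improve quality of life of cancer survivors". The same section describes the spoken interface as complementing the usual screen delivery. It also makes each participant's own earlier measurements the only comparator.

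Study itinerary says that "healthy habits, disease knowledge, self-management, QoL, and morbidity and mortality end-points will be analyzed". Primary and secondary endpoints does not list quality of life. It does list the "impact of variable modes of delivery (e.g., conversational agent) on quality of answers measure with DQS". Objectives and hypotheses explains that the DQS is there to detect inattentive or careless answering.

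**The concern.** The way the PROs are measured changes in the same phase as the intervention whose effect on quality of life is to be shown. People may answer the same item differently when speaking to an agent that helps them than when tapping a screen alone. Items on depression, anxiety or sexual function are plausible places for this. If so, the score can move although the patient has not changed, or a real change can be hidden.

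The protocol treats delivery mode as something that can affect answers, since it makes mode an object of study. It does so only for answer quality. The DQS picks up careless responding; it does not measure a shift in mean score.

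The DQS endpoint has a related difficulty. If screen delivery is seen only in T2 and T3 and agent delivery only in T4, the mode contrast is also a contrast between earlier and later months of daily questionnaires, and between different intervention phases.

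At stake are the quality-of-life claim for T4, so far as it rests on app scores, and the reading of the DQS mode endpoint.

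**Working it through.** **1. What changes between T3 and T4**

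| Feature | T2, T3 | T4 | Source |
|---|---|---|---|
| PRO answer mode | on screen, manual | free speech, agent helps | Data collection |
| Screen still used? | yes | not listed under Data collection; implied by the complementing role | Data collection; Study design |
| AI risk engine | no | yes | Study design |
| Parallel group | none | none | Study design |

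Write the mean T3-to-T4 change as true change plus mode shift. If T4 scores come only through the agent, mode and phase coincide in every participant. No mode term can then be estimated, and no analysis plan could repair that. If T4 is mixed and the mix is uncontrolled, mode is still bound up with whoever chose or was given the agent.

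**2. The plan's own figure**

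Sample size calculation gives N = 160 for a paired comparison with d = 0.25, two-sided 5% and 90% power.

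- Normal approximation: ((1.960 + 1.282)/0.25)² = 168.1, rounded up to 169.
- Paired t-test with the noncentral t: 171.
- Power at N = 160: 88.2%.

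So 160 is not reproduced exactly, although the power is within two points of 90%. That is a separate matter and nothing here rests on it. The plan's d refers to healthy habits, so 0.25 serves below only as a yardstick.

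**3. Illustration of what a mode shift would do**

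The documents give no mode shift. Assume no true change and a favourable shift of b, in SDs of the paired difference. The chance of a significant apparent improvement in a two-sided 5% paired t-test is

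P = 1 − F(t₀.₉₇₅,ₙ₋₁),

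where F is the noncentral t distribution with n − 1 degrees of freedom and noncentrality b√n. For n = 160, √n = 12.65.

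| b (assumed) | b√160 | P, n = 160 | P, n = 80 (one cancer type) |
|---|---|---|---|
| 0 | 0 | 2.5% | 2.5% |
| 0.05 | 0.63 | 9.2% | 6.4% |
| 0.10 | 1.26 | 24.1% | 14.1% |
| 0.15 | 1.90 | 47.0% | 26.3% |
| 0.20 | 2.53 | 71.0% | 42.4% |
| 0.25 | 3.16 | 88.2% | 59.8% |

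The last entry for n = 160 equals the power in step 2 by construction: a shift as large as the design effect is detected as often as the design effect.

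**4. Mixed mode**

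If a share f of the T4 answers comes through the agent, the mean shift is about f × b. With f = 0.5, b = 0.20 becomes 0.10 and P falls from 71% to 24% (ignoring any added spread). Partial exposure dilutes the problem without removing it. An unfavourable shift works the same way against a real benefit.

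**The case against.** The case on the other side is substantial, and several stronger readings that a reader might infer do not hold.

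- **That the primary endpoint is affected.** The documents do not support this. Training sessions says endpoint data are gathered at the regular follow-ups, and Study design places CASE-cancer, PAM and SUS/UEQ there. Nothing gives the agent a role in administering them.
- **That the screen is fully replaced in T4.** Data collection reads that way, but Study design gives the agent a complementing role. Exposure may be partial. This is an inconsistency to settle, not proof of a complete switch.
- **That a T3-versus-T4 test of quality of life is planned.** No such test is spelled out. Quality of life is not a listed endpoint, and Statistical analysis names CASE-cancer and SUS/UEQ for the pre, post and follow-up tests. From T3 the oncologist also chooses which PROs each patient completes and how often, so app PROs serve partly as monitoring. This lowers the weight of the point. It does not remove it, because T4 has a declared quality-of-life aim and quality of life is to be analysed.
- **That DQS items are spoken by the agent and can be failed through speech-recognition errors or passed through prompting.** The documents do not describe this. Speech recognition appears under automated classification in T2, T3 and T4, not as DQS scoring. What stands is the confounding with phase and time.
- **That the assumed shift is evidence of bias.** It is not. Its size and direction are unknown, and its upper end was set to the design effect.

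Varying the delivery mode is deliberate, and studying it is legitimate. The objection that this is a pilot on a measure outside the endpoint list is fair on severity. It is no reason to leave mode aliased with phase when this is easily avoided.

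**Conclusion.** The point holds for app-collected PROs compared across phases, and for the DQS mode endpoint. As written, a T3-to-T4 change in the QLQ-C30, PHQ-9, GAD-7 or similar app scores cannot be separated from a change of answer mode. The error could go in either direction: a mode shift may look like improvement, and the documents do not show that it will.

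On the stated assumption (0.10 to 0.25 SD of the paired difference, favourable, no true change, every scored T4 answer through the agent), an apparent improvement would be significant in about 24% to 88% of trials at N = 160, against 2.5% with no shift. With mixed mode the figures are lower.

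The conclusion about CASE-cancer, PAM and SUS/UEQ is untouched. This should be corrected, but it does not threaten the primary analysis.

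**What to change.** 1. Reconcile Data collection with Study design: state whether on-screen entry continues in T4 and for which instruments.
2. At each follow-up (T2, T3, T4), have any app PRO score that will be compared across phases self-completed on screen without the agent. Use agent-collected PROs in T4 for monitoring only.
3. For the DQS endpoint, deliver the same items by screen and by agent during T4, in random order within patient, so that mode is compared within one phase.

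Cost: items 1 and 2 are protocol wording and an app setting, at follow-ups that already exist. Some on-screen completions in T4 slightly reduce exposure to the agent. Item 3 needs some added app configuration to schedule and record the delivery mode.
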